# The Radical Extent of lymphadenectomy — D2 dissection versus complete mesocolic excision of LAparoscopic Right Colectomy for right-sided colon cancer (RELARC) trial: study protocol for a randomized controlled trial

**DOI:** 10.1186/s13063-016-1710-9

**Published:** 2016-12-08

**Keywords:** Colon cancer, Laparoscopic right colectomy, Complete mesocolic excision, Oncological outcome

## Abstract

**Background:**

The extent of lymphadenectomy during laparoscopic right colectomy can affect the oncological outcome and the safety of surgery. The principle of complete mesocolic excision (CME) has been gradually accepted and increasingly applied by colorectal surgeons. The aim of this study is to investigate whether extended lymphadenectomy (CME) in laparoscopic colectomy could improve the oncological outcomes of patients with right-sided colon cancers, compared with D2 lymphadenectomy.

**Methods/design:**

The Radical Extent of lympadenectomy: D2 dissection versus complete mesocolic excision of LAparoscopic Right Colectomy for right-sided colon cancer (RELARC) study is a prospective, multicenter, randomized controlled trial in which 1072 eligible patients with right-sided colon cancers will be randomly assigned to the CME group or the D2 dissection group during laparoscopic right colectomy. Inclusion criteria are locally advanced colon cancers situated from the cecum to the right third of the transverse colon and clinically staged as T2-4aN0M0 or TanyN + M0. The primary endpoint of this trial is 3-year disease-free survival. Secondary endpoints include 3-year overall survival, postoperative complication rates, perioperative mortality rates, and rates of positive central lymph nodes (the station 3 nodes).

**Discussion:**

The RELARC trial is a prospective, multicenter, randomized controlled trial that will provide evidence on the optimal extent of lymphadenectomy during laparoscopic right colectomy in terms of better oncological outcome and operation safety.

**Trial registration:**

ClinicalTrials.gov: NCT02619942. Registered on 29 November 2015.

**Electronic supplementary material:**

The online version of this article (doi:10.1186/s13063-016-1710-9) contains supplementary material, which is available to authorized users.

## Background

Colorectal cancer is one of the most common malignant diseases worldwide. In China, both the incidence and mortality of the disease have been increasing during the past decades, due to the aging population, changing lifestyles, and eating habits. In 2011, an estimated incidence of 23.03/10 million was reported in China, accounting for the fourth most common type of malignant tumor. With a mortality rate of approximately 11.11/10 million, colorectal cancer was the fifth leading cause of cancer-related death in China [1].

Since Hohenberger first proposed the concept of complete mesocolic excision (CME) in 2009, the principle of CME has been gradually accepted and increasingly applied by colorectal surgeons as an optimal colectomy approach for colon cancer [2, 3]. According to this principle, the extent of lymphadenectomy of the radical right colectomy is similar to that of D3 lymph node dissection, which was advocated by the Japanese Society for Cancer of the Colon and Rectum (JSCCR) in the twentieth century [4]. In CME, the central vascular ligation (CVL) enables more radical removal of the metastatic lymph nodes. The resection in the mesocolic plane guarantees radical excision of the tumor and the potential vascular or neural infiltration in the whole regional draining area, which theoretically would improve the oncological outcome in comparison with the conventional right colectomy with D2 lymphadenectomy. However, compared to D2 dissection, laparoscopic CME or D3 dissection imposes a longer learning curve for the surgeons and a higher surgery-related risk for patients due to the complicated surgical anatomy involved in the laparoscopic approach, especially the dissection in the vicinity of the superior mesenteric vessels [5–8]. Neither the National Comprehensive Cancer Network (NCCN) guidelines nor the European Society for Medical Oncology (ESMO) guidelines have clearly defined the extent of lymphadenectomy of the radical right colectomy [9]. D3 lymphadenectomy was also advocated for locally advanced colorectal cancer by the Chinese standard for diagnosis and treatment of colorectal cancer, but CME was not mentioned [10]. In addition, all the results indicating improved survival rate of CME surgery compared to traditional D2 dissection were drawn from retrospective studies [2, 11–15]. Therefore, a well-designed prospective clinical trial is crucial to investigate the optimal extent of lymphadenectomy of laparoscopic right colectomy for right-sided colon cancer. The study protocol has been written in accordance with the Standard Protocol Items: Recommendations for Interventional Trials (SPIRIT) checklist (see Additional file 1).

## Methods/design

### Study design

This study is a superiority trial. The main objective is to investigate whether extended lymphadenectomy (CME) in laparoscopic colectomy could improve the oncological outcomes of patients with right-sided colon cancer, compared to laparoscopic colectomy with D2 lymphadenectomy.

The study design is a prospective, multicenter, randomized, two-arm, parallel-group, single-blind clinical trial. The enrolled participants with right-sided colon cancers, including cancers situated from the cecum to the right third of the transverse colon, will be divided into two groups: the laparoscopic CME group (the intervention group) and the laparoscopic colectomy with D2 dissection group (the control group).

According to the final pathological results of surgical specimens, patients with stage III colon cancer or stage II disease with unfavorable histological features will be required to undergo adjuvant chemotherapy for 6 months. The oxaliplatin-based combination regimen will be recommended.

All the patients will be followed up regularly for at least 5 years, according to the follow-up protocol recommended by the NCCN guidelines. All patients are required to undergo postoperative examinations every 4 months for the first 2 years and every 6 months thereafter until 5 years after the surgery. Signs of suspected disease relapse including local recurrence (LR) or distant metastasis (DM) will be closely observed and monitored. The schedule of this trial is shown in Table 1.

**Table 1 Tab1:** Schedule of enrollment, intervention, and assessments for the RELARC trial

	Study period										
	Enrollment	Allocation	Post-allocation								Close-out
Timepoint	–2 weeks	0	Surgery	4 months	8 months	1 year	16 months	20 months	2 years	30 months	3 years
Enrollment:											
Eligibility screen	X										
Informed consent	X										
Allocation		X									
Interventions:											
Laparoscopic D2 operation			X								
Laparoscopic CME operation			X								
Assessments:											
Disease-free survival				X	X	X	X	X	X	X	X
Overall survival				X	X	X	X	X	X	X	X
Postoperative complication			X								
Perioperative mortality			X								
Central lymph node assessment			X								

Our study is expected to last 7 years, including 4 years for recruiting patients and 3 years for follow-up.

### Endpoints

The primary endpoint of this trial is 3-year disease-free survival (DFS). Secondary endpoints include 3-year overall survival (OS), postoperative complication rates, perioperative mortality rates, and rates of positive central lymph nodes (the station 3 nodes).

#### Definition of some postoperative complications

Anastomotic leak, postoperative diarrhea, and chylous ascites are possible postoperative complications. Anastomotic leak is described as the presence of luminal contents through a drain or wound site or an abscess cavity causing inflammation (i.e., fever, leukocytosis, or fecal discharge). An anastomotic leak may be detected using radiologic studies, but it must exhibit clinical signs of leakage to be considered a clinical leak.

Postoperative diarrhea shows abnormal feces, such as loose stool, watery stool, mucous stool, or bloody purulent stool three times or more a day within 2 weeks after the operation.

Chylous ascites is defined as the presence of non-infectious milky or creamy peritoneal fluid in the drainage tubes with a volume of ≥200 mL/day and a positive chyle test.

### Participating centers and investigators

Seventeen tertiary university hospitals will enroll patients in China. The surgeons who participate in the study should have experience of more than 100 cases of laparoscopic colorectal surgery per year for 2 consecutive years and the ability to complete the skilled laparoscopic CME procedure. Every investigator should provide operation videos of CME and D2 procedures within the past 3 months; these videos will be reviewed by the review committee.

### Ethical considerations

This trial protocol is approved by the Ethics Committee of Peking Union Medical College Hospital (reviewed in 2015 as ZS-851) and has been registered at ClinicalTrials.gov (identifier NCT02619942). All of the eligible participants and their legal surrogates will be fully informed of the potential risks and benefits of the interventions in each group. Only patients who are willing to provide written informed consent can be enrolled in the trial.

### Study subjects

The study subjects are patients with locally advanced right-sided colon cancers, including carcinomas located at the cecum, the ascending colon, the hepatic flexure, and the right third of the transverse colon.

The inclusion criteria are as follows:Age 18–75 years oldPathologically confirmed adenocarcinoma of right side of colonLocalization of the tumor ranging from the cecum to the right third of the transverse colonTumors clinically staged as T2-4aN0M0 or TanyN + M0, according to imaging studies including enhanced computed tomography (CT) scan, magnetic resonance imaging (MRI), etc.American Society of Anesthesiologists (ASA) score of I, II, or III.

The exclusion criteria are as follows:Synchronous or metachronous multiple primary colorectal cancerPreoperative imaging examination shows enlargement of the central lymph nodes, which mandates a D3 lymphadenectomyPreoperative imaging examination shows that the tumor involves the adjacent organs, requiring combined multiple organ resections, or radical excision (R0 resection) is not possibleHistory of any other malignant tumor in past 5 years, except for cervical carcinoma in situ that has been cured, basal cell carcinoma, or squamous cell carcinoma of skinPatients who need an emergency operationPatients who are not suitable to undergo laparoscopic surgery (due to, e.g., extensive adhesion caused by prior abdominal surgery, inability to endure artificial pneumoperitoneum, etc.).

Exit criteria include:Patients with distant metastasis that is discovered during surgical exploration or confirmed by the postoperative pathologic examinationCombined organ resection during the surgeryFusion of central lymph nodes at the mesenteric root discovered during the operation.

This study is scheduled to enroll consecutive patients in 17 tertiary medical centers in China. Patients enrolled in this clinical research will be guaranteed high-quality surgical procedures and standard medical treatment as well as convenient long-term follow-up.

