**Fig. 1 Fig1:**
[figure not shown]
D2 lymphadenectomy requires dissecting the supplying vessels right of the superior mesenteric vein (*SMV*) and keeping the covering lymphoadipose tissue of the SMV intact. **a** Right colic vein. **b** Pancreas neck. **c** Henle’s trunk. **d** Inferior pancreaticoduodenal vein. **e** Pancreas head. **f** Duodenum. **g** Undissected SMV

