### For CME procedure

In addition to the dissecting area described in the D2 procedure, the CME procedure cleans up the lymphoadipose tissue on the surface of the SMA and SMV. This requires further exposure and skeletalization of the right and anterior sides of the SMV, including the surgical trunk. This exposure should remove the lymphoadipose tissues instead of the connective tissues covering the SMA, to expose its outline (Fig. 3). Then, it is followed by the ligation of the supplying vessels (both artery and vein) at their origins; the results are shown in Fig. 4.

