### Follow-up and data collection

The postoperative examination will be performed every 4 months in the first 2 years and every 6 months in the following 3 years. Disease-free survival (DFS) is defined as the time from randomization to the time of finding the recurrence, metastasis, or death. It is calculated on a monthly basis for the latest finding. Local recurrence is defined as a recurrence of the tumor in the surgical region, with or without elevation of serum tumor markers, and the mass of the anastomotic site must be confirmed by a pathological biopsy. A distant metastasis is defined as a metastasis that is discovered in the liver, lung, bone, or other sites by CT, MRI, or radionuclide scanning, with or without pathological examination. The postoperative complications that are included in the statistics include intra-abdominal hemorrhage, gastrointestinal bleeding, anastomotic leakage, chylous fistula, surgical site infection, including intra-abdominal infections and wound infection, intestinal obstruction, postoperative diarrhea, pulmonary infection, urinary tract infection, cardiovascular accident, cerebral vascular accident, and thrombotic disease.

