### Sample size calculation

Previous retrospective studies reported that the 3-year DFS for the D2 operation ranged from 66.7% to 82.1%; the range was 77.4% to 89.1% for the CME operation [10, 15]. We estimate that the 3-year DFS for D2 and CME will be 72.0% and 80.0% respectively in this study. We expect to detect a difference of 8% in 3-year DFS between the two groups. Thus, with a significance level of 5%, a two-sided test, and 80% power, 447 patients will be required for each group. With a drop-out rate of 20%, the required sample size is 1072 patients for both arms.

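### The exit criteria can remove randomised patients for findings made during or after the allotted operation, and at least one of them, fused central nodes, lies in the field where the two arms differ

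*Protocol article*

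**What the plan says.** **Timing.** In the protocol article, Table 1 (Study design) puts allocation at time 0, ahead of the surgery column. Under Follow-up and data collection, DFS "is defined as the time from randomization to the time of finding the recurrence, metastasis, or death".

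**Exit criteria.** Study subjects lists these separately from the preoperative exclusions. There are three:
- "distant metastasis that is discovered during surgical exploration or confirmed by the postoperative pathologic" examination;
- combined organ resection during the surgery;
- fusion of "central lymph nodes at the mesenteric root discovered during the operation".

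**The field where the arms differ.** The Surgery section names dissection at the root of the mesocolon as a main difference between the groups. D2 means "keeping the covering lymphoadipose tissue of the SMV intact" (Fig. 1), whereas "the CME procedure cleans up the lymphoadipose tissue on the surface of the SMA and SMV" (For CME procedure).

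**Blinding.** Randomization and blinding says that surgeons cannot be blinded and that results are assessed by blinded independent researchers.

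**Analysis.** Statistical analysis names Kaplan-Meier and the log-rank test. The article does not say what happens to an exited patient's follow-up or data.

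**The concern.** A patient who meets an exit criterion has already been randomised and is already on the DFS clock. If such patients leave, the arms compared are those that remain after selection on events that follow randomisation. That does no harm to the comparison if the same kind of patient exits equally often in both arms. It biases the comparison if the chance of exit depends on the arm and exited patients have a different prognosis. Patients with fused central nodes would be expected to do worse than average.

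At stake is the primary DFS comparison and, with the same removals, OS and complications. The bias does not shrink with more patients, and the log-rank test cannot correct it.

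**Working it through.** **1. Does each criterion depend on the arm?**

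- *Fused central nodes.* This is the best-supported case. The finding is made at the mesenteric root, which CME opens and clears and D2 leaves covered at the vein, so CME may detect more. Against that, the exclusion criteria say that centrally enlarged nodes on preoperative imaging mandate a D3 dissection. By the same logic, fusion found at surgery conflicts with a D2 assignment but not with CME, whose nodal extent is D3 (Surgery section). D2 patients may therefore have more reason to exit. The two forces pull in opposite directions, so the sign is unknown.
- *Combined organ resection.* This is an act during surgery by an unblinded surgeon, and the Background describes CME as carrying higher surgical risk. Arm dependence is plausible, but no passage documents it.
- *Distant metastasis.* Metastasis seen at exploration comes before the operations diverge. Pathology of central tissue yields positive station 3 nodes, which are a secondary endpoint and not an exit. Arm dependence is not shown.

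**2. The plan's own figure.** The Sample size calculation states: "We estimate that the 3-year DFS for D2 and CME will be 72.0% and 80.0% respectively in this study"; and "with a significance level of 5%, a two-sided test, and 80% power, 447 patients will be required for each group". The pooled two-proportion formula for 72% versus 80% gives 447 per group, and 447 per group gives 80.1% power. The figure reproduces.

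**3. Size of the bias.** The article gives neither exit rates nor the prognosis of exited patients, so both are assumed.

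Inputs:
- n = 447 per arm;
- no true effect, with 3-year DFS p = 76% among all randomised patients in both arms (the midpoint of 72% and 80%);
- 3-year DFS among exited patients q = 40% or 20%;
- exit share f in each arm.

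DFS among those who remain = (p − f·q)/(1 − f).

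Worked example, q = 20%, exits of 5% versus 3%:
- (0.76 − 0.05 × 0.20)/0.95 = 0.7895
- (0.76 − 0.03 × 0.20)/0.97 = 0.7773
- False difference = 1.2 points.

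The rejection rate is that of the two-sided 5% two-proportion test with 447 per arm. In each range the first value is for q = 40% and the second for q = 20%.

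| Exits, one arm vs other | False difference (points) | Two-sided error |
|---|---|---|
| 5% vs 5% | 0 | 5.0% |
| 4% vs 3% | 0.4–0.6 | 5.2–5.5% |
| 5% vs 3% | 0.8–1.2 | 5.9–7.3% |
| 3% vs 0% | 1.1–1.7 | 6.8–9.4% |
| 5% vs 0% | 1.9–2.9 | 10–18% |

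The sign follows the arm with more exits: that arm looks better than it is.

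**4. With the planned effect present.** If only D2 loses such patients, 3% exits reduce the 8-point difference to 6.4–7.0 points and power to 62–70%; 5% exits reduce them to 5.3–6.3 points and 47–61%. These are one-arm extremes.

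**The case against.** The strongest objection is that the article never defines exit as leaving the analysis. It names no analysis population, and a full protocol or SAP that is not shown may keep these patients; if so, the bias disappears. This stands in part. A reader might infer that the comparison is already no longer between randomised groups, but the text does not establish that. What it does establish is a stated rule whose ordinary meaning is departure from the study. If follow-up stops at exit, no later analysis plan can recover the missing DFS times.

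Other strong readings are tempting and should not be made:
- *That pathology makes the metastasis criterion arm-dependent.* The criterion concerns distant metastasis, and positive central nodes are an endpoint.
- *That combined organ resection hides CME injuries.* The matching preoperative exclusion concerns tumour involving adjacent organs, so the natural reading is the same condition found at surgery. No passage describes an injury leading to resection and exit.
- *That the unblinded surgeon decides the exit.* The surgeon is unblinded and operates, but the article does not say who decides.
- *That the abstract contradicts Table 1 on timing.* Its wording, that patients "will be randomly assigned to the CME group or the D2 dissection group during laparoscopic right colectomy", may simply describe the dissection. Table 1 is clear.
- *That the one-arm scenarios are estimates.* All three criteria apply to both arms, so 5% versus 3% is a fairer illustration than 5% versus none.

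It is also fair to say that D2 dissects to the right of the vein and over the pancreatic head and neck, so gross fusion need not go unseen there. The imaging exclusions should also make exits fewer. Both points reduce the likely size, but neither makes the chance of exit equal between arms.

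**Conclusion.** The concern holds, chiefly for fused central nodes. The protocol sets post-randomisation exits, at least one of which lies in the field that distinguishes the arms, under an unblinded operator and with nothing that keeps the patient in the comparison. The direction cannot be told from the document.

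On the assumptions above, a modest imbalance (5% versus 3%) is a small distortion of about one point against an 8-point target, with error slightly above 5%. A one-sided 5% exit rate would be serious, with up to 2.9 points and 18% error. Equal exits of patients with equal prognosis would give no bias. The conclusion depends on exit meaning removal from follow-up or analysis, which is the natural reading but not an express statement. The stated 447 per group is not in question.

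**What to change.** State in the protocol that a patient who meets an exit criterion after randomisation stays in follow-up and is analysed in the randomised arm for DFS, OS and complications. Tabulate exits by arm and reason. Make the analysis without these patients a sensitivity analysis. This concerns follow-up and analysis only and leaves the conduct of the operation untouched.

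The cost is a wording change, continued follow-up of what is probably a small share of patients, and slight dilution. Suppose 3% of each arm has metastatic disease and is kept as events, and 80% and 72% hold for the rest. DFS then becomes 0.97 × 80% = 77.6% and 0.97 × 72% = 69.8%, a difference of 7.8 points, and power at 447 per arm is about 75% instead of 80%.

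Releasing the allocation only after exploration would turn findings visible at that stage into pre-randomisation exclusions and avoid part of that dilution. It is an optional design choice, not a correction.

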### Randomization and blinding

Patients enrolled in this study will be randomly assigned into either the study group or the control group. The random numbers are generated using Statistical Analysis System (SAS) software to ensure that patients are randomly divided into two groups with an allocation ratio of 1:1. A central randomization system will be employed, and all the researchers must register at the website of the research system. When a researcher has chosen a certain patient, he/she should log on to the webpage and upload the basic information on the patient before acquiring the random grouping schemes.

All the patients are blinded to the surgical approach that they are going to receive, and will be required to sign the informed consent before being enrolled in the study. Obviously, it is impossible to blind the surgeons who will perform the surgeries. However, all the surgeon researchers will be required to limit potential co-interventions as much as possible. In addition, the result assessment will be made by independent researchers who are blinded to the surgical procedures.

